# Preoperative smoking cessation program in patients undergoing intermediate to high-risk surgery: a randomized, single-blinded, controlled, superiority trial

**DOI:** 10.1186/s13063-022-06628-8

**Published:** 2022-08-29

**Keywords:** Randomized controlled trial, Smoking cessation, Surgery, Complications

## Abstract

**Background:**

At present, effectively implementing smoking cessation programs in the health care system constitutes a major challenge. A unique opportunity to initiate smoking cessation focuses on smokers scheduled for surgery. These patients are not only highly motivated to quit smoking but also likely to benefit from a reduction in postoperative complications which may translate into a decrease of costs. Nevertheless, surgical patients are not routinely informed about the benefits of preoperative smoking cessation. Potential reasons for this missed opportunity may be the lack of time and training of surgeons and anaesthesiologists. We therefore aim to analyse the impact of a preoperative high-intensity smoking cessation intervention on surgical complications up to a 90-day postoperative period in patients of various surgical disciplines. The hypothesis is that a preoperative smoking cessation program improves outcomes in smokers undergoing intermediate to high-risk surgery.

**Methods:**

The present study is a single-centre, randomized trial with two parallel groups of smokers scheduled for surgery comparing surgery alone and surgery with preoperative smoking cessation. We plan to randomize 251 patients. The primary objective is to compare complications between patients with an institutional multifaceted smoking cessation intervention starting 4 weeks before surgery compared to patients in the advice-only group (control group) within a 90-day postoperative period. The primary endpoint is the Comprehensive Complication Index (CCI®) within 90 days of surgery. Secondary outcomes include the length of hospital stay, cost of care, quality of life, smoking abstinence, and reduction in nicotine consumption.

**Discussion:**

The hypothesis is that a preoperative smoking cessation program improves outcomes in smokers undergoing surgery.

**Trial registration:**

BASEC #2021-02004; ClinicalTrials.gov: NCT05192837. Registered on January 14, 2022.

**Supplementary Information:**

The online version contains supplementary material available at 10.1186/s13063-022-06628-8.

## Administrative information

Note: the numbers in curly brackets in this protocol refer to SPIRIT checklist item numbers. The order of the items has been modified to group similar items (see http://www.equator-network.org/reporting-guidelines/spirit-2013-statement-defining-standard-protocol-items-for-clinical-trials/).

## Introduction

### Background and rationale {6a}

One quarter of the Swiss population smokes daily [1]. Smoking is one of the most important and few modifiable risk factors associated with cardiovascular or pulmonary diseases and cancer. Therefore, smoking cessation represents an important intervention in health care [2, 3]. At present, effectively implementing smoking cessation programs in the health care system constitutes a major challenge. A unique opportunity to initiate smoking cessation focuses on smokers scheduled for surgery. These patients are not only highly motivated to quit smoking [4] but also likely to benefit from a reduction in postoperative complications of 40% which may translate into a decrease of costs by 10% [5–7]. Nevertheless, surgical patients are not routinely informed about the benefits of preoperative smoking cessation. Potential reasons for this missed opportunity may be the lack of time and training of surgeons and anesthesiologists [8].

A systematic Cochrane review including 13 trials [7] concluded that preoperative smoking interventions increase short-term smoking cessation and reduce postoperative complications. The strongest signal was observed in two studies which performed an “intense smoking cessation program” including weekly face-to-face or telephone counselling over a period of at least 4 weeks prior to surgery. However, previous studies only reported postoperative complications up to a 30-day postoperative period and complications were not graded by severity. Additionally, most studies were performed in orthopaedic departments and therefore limiting the generalizability of its results.

We therefore aim to analyse the impact of a preoperative high-intensity smoking cessation intervention on surgical complications up to a 90-day postoperative period in patients of various surgical disciplines. Further advantages of our protocol represent the throughout coding and definition of postoperative complications and institutional approach. In this trial, we will report complications according to the Comprehensive Complication Index (CCI®) [9], which represents the most widely used and accepted measure of post-operative complications. Thereby, we improve reporting of postoperative morbidity since complications are graded by severity and the cumulative burden from any combination of complications is described in a single patient. Furthermore, our study will assess mid- to long-term smoking abstinence during follow-up to assess the impact of a preoperative non-physician-triggered smoking cessation program from a public health perspective.

### Objectives {7}

#### Hypothesis and primary objective

The hypothesis is that the preoperative smoking cessation program improves outcomes in smokers undergoing surgery. The primary objective is to compare complications between patients with an institutional multifaceted smoking cessation intervention compared to patients in the advice-only group (control group) within a 90-day postoperative period.

### Trial design {8}

This investigation is a monocentric, randomized, single-blinded, controlled superiority trial involving patients undergoing intermediate and high-risk surgery [10] at the Hospital of Lucerne. Patients will be randomised in a 1:1 ratio to either the intervention or control group. Before randomisation patients will be pre-stratified for age (≤60, >60 years) and procedure (intermediate versus high-risk procedures). Minimization, as an efficient way to control for confounding in small to moderately sized trials, will be used. Also, minimization automatically ensures the concealment of random allocation since there is no pre-existing randomization list.

## Methods: Participants, interventions, and outcomes

### Study setting {9}

Major urban hospital in Lucerne, Switzerland

### Eligibility criteria {10}

#### Inclusion criteria

Patient listed for intermediate or high-risk surgery (Additional file 2) [10] at the Cantonal Hospital of LucernePatient undergoing surgery in one of the following departments: Abdominal surgery, thoracic surgery, urology, gynaecology, vascular surgery or head and neck surgeryDate of surgery >4 weeks planned after date of listing for surgery or discussion by tumor boardCurrent smokers, defined as daily smoking of at least one cigarette, cigar, or pipeAge ≥ 18 yearsAble to give signed written informed consent

#### Exclusion criteria

Consumption of illegal drugsAlcohol dependency defined as preexisting alcohol-related disorders (eg. alcoholic psychosis, alcohol abuse, alcohol polyneuropathy, degeneration of the nervous system due to alcohol, alcoholic myopathy, alcoholic liver disease)Inability to follow the procedures of the study, e.g. due to language problems, psychological disorders, dementia

### Who will take informed consent? {26a}

Patients will be contacted and informed about the study over the phone. The study nurse will explain to each participant the nature of the study, its purpose, the procedures involved, the expected duration, the potential risks and benefits and any discomfort it may entail. Each participant will be informed that the participation in the study is voluntary and that he or she may withdraw from the study at any time and that withdrawal of consent will not affect his or her subsequent medical assistance and treatment. The participant will be informed that his or her medical records may be examined by authorised individuals other than their treating physician. All participants interested in the study will be provided a participant information sheet and a consent form describing the study and providing sufficient information for the participant to make an informed decision about their participation in the study.

### Additional consent provisions for collection and use of participant data and biological specimens {26b}

No samples will be stored and therefore no additional consent is required.

## Interventions

### Explanation for the choice of comparators {6b}

Patients randomised to the control arm will get advice only. Their preoperative course will be as if they were not participating in this study, meaning they will receive inconsistent perioperative smoking cessation advice from nurses, surgeons, or anaesthesiologists but no further study-specific smoking cessation intervention. Importantly, participants in the control group will not be discouraged from using perioperative smoking cessation aids and can still obtain help on their own initiative.

### Intervention description {11a}

The study intervention consists of an interview by a Tobacco Treatment Specialist (TTS) 4 weeks before surgery with individual counselling and offered nicotine substitution. All TTS have > 15 years of experience and underwent a postgraduation course for counselling smoking cessation. The intervention meeting is based on the Chronic Care Model (CCM) [11, 12] to improve the quality of ambulatory care through six interrelated system changes [13]: self-management support, decision support, delivery system design, clinical information systems, health care organisation, and community resources. In line with the CCM, the intervention will include the following elements adapted from Haas et al. randomized clinical trial [14] and are described in the treatment plan. In brief, the intervention includes:Informative content about advantages of smoking cessation [15] using information leaflets along with decision supportScheduling service for a motivational interview by a TSS in the office to provide educational and motivational content, explain the magnitude and profile of nicotine dependence and implement a treatment plan [16]For participants willing to quit smoking a preoperative quit day will be scheduled after the first intervention meeting 2–3 weeks before surgery. Time of a preoperative quit day may vary between patients, since our smoking intervention focuses on as early quit attempts as possible. Therefore, there will be a variety in patients with one or more quit attempts, with or without success, and patients who quit smoking in the postoperative period, only.Patients will be encouraged by a TSS to use nicotine replacement with patches/gums/pills at their own discretion. For smokers of 20 cigarettes per day or more, a 4-week supply of 21mg/day, 2-week supply of 14 mg/day and a 2-week supply of 7 mg/days patches will be provided. Patients who smoke between 10 and 20 cigarettes per day will receive a 4-week supply of 14 mg/day and a 4-week supply of 7 mg/day. Smokers of <10 cigarettes per day will be supplied with a 4- to 8-week supply of 7-mg/day patches. Bupropion or Varenicillin will be provided on an individual basis (all costs are covered by the patient’s insurance).

### Criteria for discontinuing or modifying allocated interventions {11b}

Patient preference.

### Strategies to improve adherence to interventions {11c}

TSS will schedule repeated follow-up meetings to support smoking abstinence or nicotine reduction before and after surgery for all patients. However, patients not interested in further smoking cessation counselling will not be forced to participate in additional follow-up meetings.

The patient’s general practitioners will be informed about the aim of the trial by e-mail and will be asked to further support the patient regarding smoking cessation and encourage abstinence at the end of follow-up as tobacco dependence might be better viewed as a chronic disorder, requiring repeated episodes of treatment.

### Relevant concomitant care permitted or prohibited during the trial {11d}

No further concomitant care is prohibited.

### Provisions for post-trial care {30}

TSS will schedule repeated follow-up meetings to support smoking abstinence or nicotine reduction before and after surgery for all patients. However, patients not interested in further smoking cessation counselling will not be forced to participate in additional follow-up meetings.

### Outcomes {12}

The primary endpoint is the (CCI®) [9] within 90 days of surgery. The CCI is calculated as the sum of all Clavien–Dindo complications [17] (Additional file 1) that are weighted for their severity (multiplication of the median preference values from patients and physicians). The final formula yields a continuous scale that ranks the cumulative burden from any combination of complications from 0 to 100 in a single patient. As a composite complication score, the CCI has the advantage of reflecting the overall burden of the postoperative course that affects the health of patients and their quality of life. In addition, the CCI is a powerful endpoint in trials, as it allows sample size up to nine times lower compared with traditional morbidity endpoints [18]. Complications will be assessed from medical health records by an advanced nurse practitioner supported by a surgical resident and consultant, all of whom were already trained in the Clavien–Dindo classification in a pilot study. Outpatient information of complications treated at other institutions will be included.

Secondary endpoints are length and costs of hospital stay, readmission rates for inpatient hospital stay, smoking abstinence or nicotine reduction, nicotine dependence, mental health, quality of life, unplanned postoperative intermediate care or intensive care unit admissions and cost and. Secondary endpoints will be recorded up to a 12-month postoperative follow-up period and will be compared between the intervention and control group. Smoking abstinence or nicotine reduction will be assessed by measuring smoking status (cigarettes smoked per day) and nicotine dependence will be assessed using the Fagerström test [19]. Nicotine abstinence will be additionally confirmed by using the NicAlert cotinine saliva test. Quality of life will be assessed with the German version of the 36-Item Short Form Survey (SF-36; index values range from 0 to 1, with higher scores indicating better quality of life) including covering physical functioning, bodily pain, role limitations due to physical health problems, role limitations due to personal or emotional problems, emotional well-being, social functioning, energy/fatigue, and general health perceptions during the past 4 weeks [20]. Mental health will be assessed using the Hospital anxiety and depression scale (HADS) [21].

Morbidity may influence the endpoints, therefore Charlson Comorbidity Index [22] and the American Society of Anaesthesiologists (ASA) physical status classification [23] will be assessed for each patient at baseline. The following characteristics measured at baseline are further described: age, gender, surgical procedure, underlying medical conditions and the stage of the Transtheoretical Model (TTM) of behaviour change.

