### Plans for collection, laboratory evaluation and storage of biological specimens for genetic or molecular analysis in this trial/future use {33}

Nicotine abstinence will be confirmed by using the NicAlert saliva test. The test will be performed by an advanced nurse practitioner during a routine hospital visit of the participant. The NicAlert saliva test is a point of contact test detecting six ranges of cotinine concentrations from 0 to 2000+ ng/ml. The only data collected is the category of concentration. No biological samples will be stored, and no further laboratory tests will be carried out. The test kit and the saliva sample will be immediately destroyed after use.

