The Fagerström test results, the quality of life (SF-36 Index) and the smoking status (cigarettes smoked per days) will be measured repeatedly over time from baseline, and for each outcome, mixed-effects models will be used to estimate the treatment effect and also to quantify the time*treatment interaction. The result of NicAlert Saliva test between treatment groups will be evaluated by applying chi-square test.

Cost-effectiveness analyses will be performed from a health care institution as well as a population public health perspective. First, hospital costs in both arms with and without costs of the tobacco treatment specialist (TTS) consultation per session, and nicotine replacement products will be compared as averages per patient across treatment groups. Second, the incremental cost per additional quit and incremental cost per additional life year saved of the preoperative institutional smoking cessation program compared to usual care will be calculated. Utilities will be calculated based on quality-of-life measurements using the SF-36 questionnaire.

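### Cigar and pipe smokers are eligible, but amount smoked is counted only in cigarettes, so their reduction cannot be measured and their abstinence rests on the saliva test alone

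*Protocol article*

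**What the plan says.** All places are in the protocol article.

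- **Eligibility criteria {10}.** A current smoker is anyone who each day smokes one or more cigarettes, cigars or pipes.
- **Outcomes {12}.** The secondary endpoints, recorded for up to 12 months after surgery, include "smoking abstinence or nicotine reduction, nicotine dependence, mental health, quality of life". On measurement: "Smoking abstinence or nicotine reduction will be assessed by measuring smoking status (cigarettes smoked per day"). The section then adds: "Nicotine abstinence will be additionally confirmed by using the NicAlert cotinine saliva test".
- **Statistical methods {20a}.** The unit is repeated: "the smoking status (cigarettes smoked per days) will be measured repeatedly over time from baseline", analysed with mixed-effects models that include a time-by-treatment interaction. The saliva test is analysed separately: "The result of NicAlert Saliva test between treatment groups will be evaluated by applying chi-square test". The economic analysis plans "the incremental cost per additional quit and incremental cost per additional life year saved".
- **Section {33}, biological specimens.** "The NicAlert saliva test is a point of contact test detecting six ranges of cotinine concentrations from 0 to 2000+ ng/ml". Only the concentration category is kept.
- **Intervention description {11a}.** "Patients will be encouraged by a TSS to use nicotine replacement with patches/gums/pills at their own discretion". The patch supplies described there last 4 to 8 weeks.

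**The concern.** The entry rule covers three smoked products and the measure of amount covers one. This is not a detail left for later. The article fixes the unit twice, once as the outcome and once as the dependent variable of a model, and that unit does not span the population it admits.

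Two kinds of patient fall outside the measure. One smokes only cigars or a pipe, starts at zero and cannot go lower. The other starts on cigarettes and moves to cigars or a pipe, and on this measure looks the same as someone who has stopped. At stake is how the reduction analysis reads, and how far self-report can support a claim of abstinence in these patients.

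**Working it through.** **1. The plan's own figure.** No figure is given for any smoking outcome. The sample size rests on the Comprehensive Complication Index: means 13 and 5.5 (difference 7.5), SD 20, two-sided 5%, 80% power. The normal approximation is n = 2 × (1.960 + 0.842)² × 20² / 7.5² = 111.6, so 112 per arm. The t-test version gives 112.6, so 113 per arm and 226 in total, as stated. With 10% dropout, 226 / 0.9 = 251.1, stated as 251. No smoking quantity enters, so this point cannot change the sample size.

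**2. What the stated measures record.** Four example patients (20 cigarettes per day is illustrative):

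| Patient | Cigarettes/day, baseline | Cigarettes/day, follow-up | Recorded change | True state | Cotinine, no replacement | Cotinine, on replacement |
|---|---|---|---|---|---|---|
| A: pipe only, continues | 0 | 0 | 0 | smoking | raised | raised |
| B: pipe only, stops | 0 | 0 | 0 | quit | not raised | raised |
| C: 20 cigarettes, switches to cigars | 20 | 0 | −20 | smoking | raised | raised |
| D: 20 cigarettes, stops | 20 | 0 | −20 | quit | not raised | raised |

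The cotinine columns use general pharmacology: cotinine is formed from nicotine whatever its source. On cigarettes per day, A cannot be told from B, nor C from D. Off replacement, cotinine separates both pairs. On replacement it separates neither, and self-report would have to decide. For these patients self-report is zero either way.

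**3. What cotinine does not reach.** The saliva result has its own chi-square test and does not enter the cigarettes-per-day model. So the reduction analysis is not repaired even where cotinine is informative. The article states no rule for a conflict between self-report and saliva.

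**4. Size for the reduction analysis.** Let f be the share of exclusive cigar or pipe smokers, assumed equal in the two arms, and d the between-arm difference in mean change among cigarette smokers. Patients with f contribute zero change, so the expected difference over all patients is (1 − f) × d. The article gives no f; 2% to 10% is an assumption.

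| f | Patients of 226 | Expected difference |
|---|---|---|
| 2% | 0.02 × 226 = 4.5 | 0.98 d |
| 5% | 0.05 × 226 = 11.3 | 0.95 d |
| 10% | 0.10 × 226 = 22.6 | 0.90 d |

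Product switching acts differently: it overstates reduction in whichever arm switches more. Nothing in the article allows its size or direction to be estimated.

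**The case against.** The strongest reply is that cigarettes per day is not the only measure. The outcomes section adds cotinine confirmation straight after it, and a continuing cigar or pipe smoker with a positive test would not be confirmed abstinent. This stands for abstinence. It does not help with reduction, which has no cotinine analysis.

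A reader might go further and infer that exclusive cigar or pipe smokers are counted as quitters, inflating quit rates in both arms. On assumed true quit rates of 30% and 10%, that reading gives recorded rates of f + (1 − f) × true rate. At f = 5% these are 0.05 + 0.95 × 0.30 = 33.5% and 0.05 + 0.95 × 0.10 = 14.5%, so the difference falls from 20 to 19 points and the ratio from 3.0 to 2.31. The documents do not support this. Nowhere does the article say that zero cigarettes alone makes a patient abstinent, and the arithmetic sets the saliva test aside. Nor does nicotine replacement rescue the inference, because it makes a true quitter look non-abstinent rather than the reverse.

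It is likewise tempting to say that the cost per additional quit is built on the faulty measure. The article does not say which measure defines a quit. Even on the reading above, the cost per quit would change by a factor of 20/19, about 5%.

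Three further replies have some force:

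- Cigarettes per day stands in parentheses after smoking status and may be shorthand. But the methods section uses it again as the repeated outcome to be modelled.
- The analysis plan is an additional file not at hand and may define abstinence. It would still have to depart from the unit fixed here.
- Patches are supplied for at most 8 weeks and follow-up runs to 12 months, so the overlap between replacement and late saliva tests is not shown. The ambiguity is confined to periods of replacement use. It may differ by arm, since replacement is encouraged in the intervention arm, while controls may obtain aids themselves.

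**Conclusion.** The point holds in a limited form. The only stated measure of amount smoked does not fit part of the eligible population. As written, reduction cannot be measured in exclusive cigar or pipe smokers, and a switch from cigarettes to another smoked product is recorded as a fall to zero. For these patients the self-reported part of abstinence is uninformative, which leaves the saliva test alone, with its ambiguity during nicotine replacement.

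The effect is small. Under an assumed share of 2% to 10%, equal across arms, the difference in mean cigarettes per day is diluted by the same 2% to 10%; switching is unquantified. The consequences stay within secondary smoking outcomes, and reach cost per quit only if self-report defines a quit. The primary endpoint and the planned 226 and 251 patients are unaffected. An improvement worth making, not a threat to the trial.

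**What to change.** In Outcomes {12} and Statistical methods {20a}:

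1. Record use of each smoked product named in the inclusion criterion (cigarettes, cigars, pipe) at baseline and at each visit.
2. Define self-reported abstinence as no smoked tobacco of any kind, with cotinine as confirmation.
3. Analyse reduction relative to each patient's own baseline, either by product or with a prespecified cigarette-equivalent conversion. Alternatively, restrict the cigarettes-per-day model to patients who smoke cigarettes at baseline, and report product switching by arm.

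A plain sum of units should be avoided. Moving from 20 cigarettes to 3 cigars would score as (20 − 3) / 20 = 85% reduction, although the units are not comparable.

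The cost is one extra questionnaire item at visits already planned, and a short change of wording in the two sections. The restricted model drops the few exclusive cigar or pipe smokers from that one analysis, which should be stated when it is reported.
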